### 5.4.3 Interim Analysis

This project is expected to be funded by the NIMH through the R61/R33 mechanism. This mechanism has a go/no-go decision after two years (the R61 phase). For the GO criterion, we will test if mbNF leads to larger changes than control-NF (medium effect-size, Cohen's d of at least 0.5) in at least one of our two DMN connectivity targets. We will calculate within-subject change from pre- to post-NF, then use one-tailed t-tests (mbNF vs. shamNF) to test our hypothesis that mbNF will lead to larger change by decreasing within-DMN connectivity and/or increasing DMN-FPCN anticorrelation. This analysis will include all of the R61 participants who complete the neurofeedback day (n = 26 per group).

#### **5.4.4 Handling of Missing Data**

Missing data will be accommodated using multiple imputation or weighting procedures.

## **6 Trial Administration**

### **6.1 Ethical Considerations: Informed Consent/Assent and HIPAA Authorization**

Consent forms will be Institutional Review Board (IRB)-approved and the participant will be asked to read and review the document.

If a potential participant joins a first screening visit (always a live meeting, usually remote, with a [name] lab staff member), the first step will be the consent process, including a review of study overview and goals, study procedures, study risks and benefits, confidentiality, economic considerations, and in-person expectations regarding infection control for MRI days. Particular mention will be made and reviewed that participation is always voluntary, and that they may withdraw at any time without prejudice. Then the participant will have unlimited time to review the e-consent form, consult with trusted others in their life, think about it, and ask questions. Only if they decide to sign and submit the form does the visit proceed.

Upon submission, a copy of the informed consent document will be emailed to the participant/LAR for their records.

### **6.2 Institutional Review Board (IRB) Review**

The protocol will be submitted to the IRB for review and approval. Approval of the protocol must be obtained before initiating any research activity. Any change to the protocol or study team will require an approved IRB amendment before implementation. The IRB will determine whether informed consent and HIPAA authorization are required.

A study closure report will be submitted to the IRB after all research activities have been completed.

### **6.3 Subject Confidentiality**

Participant confidentiality and privacy is strictly held in trust by the participating investigators, their staff, and the sponsor(s) and their interventions. Therefore, the study protocol, documentation, data, and all other information generated will be held in strict confidence. No information concerning the study or the data will be released to any unauthorized third party without prior written approval of the sponsor.

All research activities will be conducted in as private a setting as possible.

The study monitor, representatives of the Institutional Review Board (IRB), or regulatory agencies may inspect all documents and records required to be maintained by the investigator, including but not limited to, medical records (office, clinic, or hospital) for the participants in this study. The clinical study sites will permit access to such records.

The study participant's contact information may be securely stored at each clinical site involved with the subject for internal use during the study. At the end of the study, all records will continue to be kept in a secure location for as long a period as dictated by the reviewing IRB, Institutional policies, or, if applicable, sponsor requirements.

Study participant data related to participation in the psychotherapy program will be maintained according to standard practice at the U Mass Psychological Services Center. These records will include participant identifiers and contact information.

Study participant research data, which is for purposes of statistical analysis and scientific reporting, will be transmitted to and stored at in Yale REDCap servers and on MR data servers at Yale and MGH. This will not include the participant's contact or identifying information. Rather, individual participants and their research data will be identified by a unique study identification number. The study data entry and study management systems used will be secured and password protected. At the end of the study, all study databases will be de-identified and archived electronically in Yale-maintained systems (for clinical, interview, and survey data) or Yale/MGH-maintained systems (for MR data).

#### **6.4 Deviations/Unanticipated Problems**

A protocol deviation is any noncompliance with the study protocol. The noncompliance may be either on the part of the participant, the investigator, or the study site staff. As a result of deviations, corrective actions are to be developed by the site and implemented promptly.

It is the responsibility of the site investigator to identify and report deviations within [specify number] working days of identification of the protocol deviation. All deviations must be addressed in study source documents, reported to the study sponsor, and the reviewing Institutional Review Board (IRB) per their policies.

Unanticipated problems involving risks to participants or others include, in general, any incident, experience, or outcome that meets all of the following criteria:

- Unexpected in terms of nature, severity, or frequency given (a) the research procedures that are described in the protocol-related documents, such as the Institutional Review Board (IRB)-approved research protocol and informed consent document; and (b) the characteristics of the participant population being studied;
- Related or possibly related to participation in the research ("possibly related" means there is a reasonable possibility that the incident, experience, or outcome may have been caused by the procedures involved in the research); and
- Suggests that the research places participants or others at a greater risk of harm (including physical, psychological, economic, or social harm) than was previously known or recognized.

The investigator will report unanticipated problems (UPs) to the reviewing Institutional Review Board (IRB) and to the study sponsor. The UP report will include the following information:

- Protocol identifying information: protocol title and number, PI's name, and the IRB project number;
- A detailed description of the event, incident, experience, or outcome;
- An explanation of the basis for determining that the event, incident, experience, or outcome represents an UP;
- A description of any changes to the protocol or other corrective actions that have been taken or are proposed in response to the UP.

To satisfy the requirement for prompt reporting, UPs will be reported using the following timeline:

- UPs that are serious adverse events (SAEs) will be reported to the IRB and study sponsor, if applicable within [insert timeline in accordance with of the investigator becoming aware of the event.
- Any other UP will be reported to the IRB and study sponsor within 5 days of the investigator becoming aware of the problem.
- All UPs should be reported to appropriate institutional officials (as required by an institution's written reporting procedures), the supporting agency head (or designee), and the Office for Human Research Protections (OHRP) within & [insert timeline in accordance with policy] of the IRB's receipt of the report of the problem from the investigator.
- 

## 6.5 Data Safety Monitoring Plan

### Summary of the protocol

This is a clinical trial where 124 adults with borderline personality disorder (52 in the R61 phase) will participate in an intervention that combines psychotherapy and mindfulness-focused real time fMRI neurofeedback (mbNF). Subjects will be randomized to receive either this mbNF targeting Default Mode Network connectivity (the experimental intervention) or yoked sham feedback (the control intervention). All subjects must be 18-60 years old, have BPD, no primary psychotic disorder, no bipolar disorder, no cognitive or learning disorder or serious head injury, no serious substance use disorder in last 6 months, be safe for and able to tolerate an MRI. Medications must be kept constant during the whole study. Subjects and clinical staff are blind regarding which group they are assigned to. We assess whether the experimental intervention yields greater improvements in emotion regulation and greater symptom improvements than the control intervention. We also assess changes in functional connectivity induced by the intervention and their relationships to changes in mindfulness and clinical symptoms.

Roles and Responsibilities: [name], [name], and the Yale Human Research Protection Program (HRPP) will work together to monitor the safety of subjects at the Yale site. Yale will serve as the single IRB for the whole study. [name] and MGH clinician [name] MSW will monitor the safety of subjects during in-person scan days at the MGH site, and remain in close contact with the whole leadership team about any concerns. [name] team at U Mass Amherst will see the study subjects in remote DBT skills group each week and will raise any concerns with the rest of the study leadership team. In addition to day-to-day oversight, [name] will formally review all the clinical assessments on a quarterly basis to identify any potentially concerning patterns. The clinical raters and therapy teams will be blinded to subject group (mbNF or shamNF), but the neurofeedback staff ([name], [name] and the at-scanner research assistants) will not be blinded, so they will review the study data quarterly as well to identify any potentially concerning patterns by group. A DSMB will be constituted by the study leadership team in consultation with the Program Officer in order to ensure that people with expertise in BPD and clinical trials are at the table. The study leadership team (Drs. [name], and as needed, Drs. [name], [name], [name], and [name]) will meet with the DSMB every six months to review all clinical data and discuss any potential clinical safety issues. The study staff that collect adverse events information will report serious and adverse events and UPIRSOs immediately to [name] who will review them to determine if further action is necessary. If there is any doubt, they will be discussed with the DSMB and IRB and officially reported and handled as recommended.

Any unanticipated or serious adverse events will be reported immediately to [name] who will report them to the NIH as required. Unanticipated or serious events will also be discussed immediately by [name] and [name], including the rest of the leadership team as needed, to assess their likelihood of being related to the intervention and to determine, in consultation with the IRB, if the study protocol should be modified or stopped.

Our team is experienced in the management of clinical risk in BPD in both clinical and clinical research settings. The clinical ([name]) and clinical assessment ([name]) leaders on this project will work together with the study team, a DSMB, and the Yale IRB to ensure careful monitoring and decision-making and to ensure that known risks (including self-harm, safety in the MR scanning environment, data privacy, and other clinical developments requiring a change of care), as well as any unexpected safety issues that may arise, are appropriately managed.

**Trial Safety:** The full study team will be responsible for maintaining confidentiality and security of all the data collected in the study, and for ensuring safety in the study. [name] will take primary responsibility for safety at the Yale site, and [name] will take primary responsibility for safety at the MGH site. [name] will also take responsibility for the overall management of safety across all sites. The imaging centers at both Yale and MGH have established protocols for imaging safety that have been used effectively for many years. Drs. [name] and [name] will ensure that all study staff are well-trained in these safety protocols and committed to following them at their respective sites. In terms of privacy, all assessments will be conducted in private rooms, remote clinical sessions will be conducted over secure platforms, electronic data will be stored on firewall protected computers, and paper data will be stored in locked file cabinets in locked offices, and only accessible to approved study personnel. In terms of medication or treatment needs, if a situation arises in which a patient becomes clinically unstable and requires (or strongly desires) a change in medication or other treatment intervention that is a contraindication to ongoing study participation, they will pursue the required intervention through standard channels (i.e. their established providers), without any restrictions deriving from study participation. The decision to exclude them from the study will be made on a case-by-case basis by the study leadership team, blind to neurofeedback condition.

At each study assessment session, staff will collect adverse event info as well as clinically evaluating the patient. Any nontrivial clinical decline, or any serious adverse event, will be brought to the attention of the clinical team within 24 hours. [name] will be available throughout the study to field any questions or clinical concerns that may arise. These mechanisms – regular assessments, on-call availability, and direct coordination between the study clinical team (Drs. [name] and [name]; [name]) – will be used to manage any unexpected clinical situations that may arise, and to make decisions with the patient regarding any decision to withdraw from the protocol. If withdrawal from the study is necessary, we will provide appropriate referrals for other treatments. Incidental findings in the MR scanning session will be shared with a neuroradiologist at the relevant site, who will decide whether subjects should be notified and whether clinical follow-up is recommended.

Conflicts of interest (COI) are regularly monitored. The investigators do not currently have any COI of relevance to this study. However, if any unforeseen COI do develop, they will be reported to Yale and managed as recommended.

**Reportable events:** Suspension or termination of the protocol will be reported to NIH within 3 business days, along with an explanation. The death of a subject will be reported to NIH within 5 business days of the PI learning of it. Any unanticipated problems involving risks to subjects or others that are related or possibly related to participation will be reported within 7 days of the team becoming aware of the event. Any noncompliance the internal review board considers to be serious or continuing will be reported within 10 days to NIH. All adverse events and protocol violations in the study will be summarized in the yearly reports, including the renewal of the human subjects protocol of that site, and the annual progress

report to NIH. Documentation of reportable events will include identifying information for the research protocol, date of event, date when PI became aware of event, detailed description and impact of event on subject (or other), summary of any measures taken and required reports made to regulatory bodies, as well as any changes in the protocol or other corrective actions taken.

Data management, analysis and quality assurance: Data collected will include personal health information, clinical assessments and MR imaging data. All assessments will be conducted in private rooms, electronic data will be stored on firewall protected computers, and paper data will be stored in locked file cabinets in locked offices, and only accessible to approved study personnel. All personnel will be trained to follow HIPAA regulations. The full study team will be responsible for overseeing quality assurance in the data, which will involve cross-checking data records with original sources and verifying accurate data analyses.

Risks associated with the current study are deemed greater than minimal for the following reasons:

The proposed study involves greater than minimal risk because the subject population (adults with Borderline Personality Disorder) has a higher than average frequency of self-harm and because this study involves a treatment intervention. Given the established safety of both fMRI neurofeedback and DBT skills group, we do not view the proposed study as high risk.

Although we have assessed the proposed study as one of greater than minimal risk, the potential exists for anticipated and/or unanticipated adverse events, serious or otherwise, to occur since it is not possible to predict with certainty the absolute risk in any given individual or in advance of first-hand experience with the proposed study methods. Therefore, we provide a plan for monitoring the data and safety of the proposed study as follows:

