#### 4.3.2 Eligibility Criteria/Vulnerable Populations

As above, we plan for 124 people to complete the overall study. We expect that enrollment will be balanced between the New Haven and Boston cohorts, for a total of 62 participants per site. This means that we expect a final total of 31 completers randomized to each group (mbNF and control NF) at each site at the end of the study.

This study is open to people of any sex at birth and any gender.

**Inclusion criteria.** All subjects must: be age 18-60, be able to provide written informed consent, meet criteria for BPD on semi-structured clinical interview, be able to plan to keep any prescribed medications and psychotherapy constant during the study, and be fluent in English.

**Exclusion criteria.** Potential subjects will be excluded for:

- current DBT psychotherapy outside the study
- lifetime primary psychotic disorder or Bipolar I disorder
- developmental disorder (e.g. autism)
- history of learning disorder
- moderate or severe substance use disorder in the last 6 months
- active suicidal ideation with intent or plan in the past 3 months
- history of major medical or neurologic disorder
- MRI contraindications, including pregnancy
- poor performance on reading task (WRAT > 11 errors)
- newly prescribed medications in the past 8 weeks
- daytime sedating medications (e.g. benzodiazepines, opiates, sedating neuroleptics)
- any scheduled daily benzodiazepines
- change in psychotherapy type or frequency in the past 12 weeks.
- At the discretion of the study PI

*Termination criteria.*

- Enrolled participants will be terminated from DBT group participation for:
  - Missing over 3 consecutive DBT group sessions. These participants will still be invited to complete study assessments.
- Enrolled participants may be terminated from the study:
  - At the discretion of the study PI

Eligibility will be determined by study personnel.

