**Medication considerations.** Medication use is common in our target sample. Though adding some complexity, allowing medication will increase representativeness and generalizability. We will require that study participants not be taking daytime sedating medications. Treatment prior to and during the study will be recorded and explored in analyses. We will code medications into 5 classes: antidepressants, antipsychotics, mood stabilizers, anxiolytics, stimulants. We check if overall binary medication variables (psychotropic medication or not) or class-level medication binary variables (presence/absence of each medication class) differ between groups and if so, we will include them as covariates in the statistical analyses.

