### Clinical Baseline and Follow-up Assessments

Clinical and demographic measures will be collected at baseline, before and after the neurofeedback day, at the start of each DBT module, and at each of the two follow-up timepoints.

Demographic data (including age, years of education, ethnicity, occupation, hours per week working, and relationship status) as well as medical history, psychiatric history, current medication list, and adherence will be collected from all participants who give consent. Should we decide to, in order to pursue specific questions of task performance in specific groups, we will use these screens to enroll specific balanced groups of people with specific demographics, such as limited age range, gender, or medications.

All enrolled participants will complete several psychological questionnaires.

[figure not shown]

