### **Psychotherapy (DBTsg)**

DBTsg will be a weekly 2-hour group that subjects join by secure videoconference (e.g. Zoom) through the UMass Psychological Services Center. DBTsg will follow the 20-week McMain protocol which led to improvement in treatment > control patients on emotion regulation, distress tolerance, anger, and suicidal/self-harming behaviors. Each subject cohort will proceed through the McMain-protocol DBT modules: Distress Tolerance (4 sessions including skills for “crisis survival,” “distracting,” and “radical acceptance”), Dialectics (4 sessions, including skills for validation, “walking the middle path,” and increasing positive behaviors), Emotion Regulation (4 sessions, including skills for observing and describing emotions, reducing vulnerability to negative emotions, and “opposite action”), and Interpersonal Effectiveness (4 sessions, including skills for clarifying priorities in interpersonal situations, relationship effectiveness, and maintaining self-respect). Each module is preceded by one week focused on mindfulness. We selected this protocol because it is the longest of the evidence-based skills group protocols, with 5 full months of treatment (approaching the 6-month classical schedule).

The DBT groups for this study will be directed by [name], who is a clinical psychologist licensed in CT and MA, certified DBT trainer who routinely supervises doctoral students in DBT. We expect this treatment dose to provide meaningful benefit to patients while also facilitating our study design. Admission to the DBTsg program will be rolling, with new subjects admitted on the mindfulness day at the beginning of each module. DBTsg will run continuously throughout the year so subjects can join at the beginning of any module and graduate once they have participated in four full modules. In this way, we can stagger subjects to facilitate the scheduling of NF scans and complete a full cohort.

All DBTsg zoom sessions will be recorded, and participants must agree to video recording in order to be included in the study.

Before, during, and after psychotherapy, mental healthcare use and needs will be tested as exploratory outcomes:

a) (for during study psychotherapy) DBTsg group attendance (scored by study staff by watching videos)

b) use of scheduled and unscheduled mental healthcare resources outside the study (question included in surveys at each assessment timepoint)

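### A patient excluded from the study after clinical instability has no stated route to the week-16 BSL-23, so the primary clinical outcome can be lost for a reason tied to that outcome

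*Protocol*

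**What the plan says.** The Trial Safety paragraph of section 6.5 (Data Safety Monitoring Plan) concerns a patient who becomes clinically unstable and requires, or strongly desires, "a change in medication or other treatment intervention that is a contraindication to ongoing study participation". Treatment is then sought through the patient's own providers. On study status it says: "The decision to exclude them from the study will be made on a case-by-case basis by the study leadership team, blind to neurofeedback condition". Later in section 6.5, the only provision for a withdrawn patient is this: "If withdrawal from the study is necessary, we will provide appropriate referrals for other treatments".

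The termination criteria in section 4.3.2 have two tiers. The first is removal from the DBT group for more than three consecutive missed sessions, and for it the protocol adds: "These participants will still be invited to complete study assessments". The second begins "Enrolled participants may be terminated from the study" and leaves the matter to the investigator's discretion. It carries no such sentence.

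Section 5.4.1 sets the primary clinical outcome as change in BSL-23 from pre-NF to DBT week 16, analysed with a mixed model. Section 5.4.4 handles missing data by multiple imputation or weighting. The assessment schedule in section 5.1 reads: "Clinical and demographic measures will be collected at baseline, before and after the neurofeedback day, at the start of each DBT module", followed by the two follow-up timepoints.

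**The concern.** The protocol separates stopping treatment from stopping measurement for patients who miss sessions. It does not do so for patients who leave because they deteriorated, whose exit is most closely tied to the outcome. If such a patient is excluded before week 16 and assessments stop, the missing BSL-23 is likely to be a poor one.

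A decision made blind to arm prevents deliberate selection by arm, but it does not make the missingness unrelated to outcome. If mbNF works, fewer mbNF patients cross any given threshold of deterioration, so an identical rule removes more controls. The control mean then looks better than it was, and a real benefit is understated. Replacing dropouts (section 4.3.1) restores the number of patients but not the lost scores.

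The gap has to be closed in the protocol, because no analysis plan can recover scores that were never collected.

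**Working it through.** **The plan's own figure.** Section 5.4.1 gives f = 0.15, 62 per group (N = 124), m = 2 timepoints, correlation 0.3, alpha 0.05 and 80% power.

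- lambda = f² × N × m / (1 − rho) = 0.0225 × 124 × 2 / 0.7 = 7.97. With 1 and 122 degrees of freedom, power = 0.80. The stated figure reproduces.
- The same effect in SDs of change: sqrt(7.97) × sqrt(2/62) = 2.823 × 0.1796 = 0.51. This is the true effect used below.

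**Scale of exclusion (assumed).** Section 5.4.1 expects about 30% loss, so 124 / 0.70 ≈ 177 enrolled and about 53 lost from all causes. The protocol does not say how many of these would leave by the section 6.5 route. Taking 5%, 10% and 15% of 177 gives about 9, 18 and 27 patients.

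**Timing of scores.** Each DBT module is one mindfulness week plus four sessions, or five weeks. Module starts therefore fall at weeks 1, 6, 11 and 16. The last score before the endpoint is at week 11.

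**Simulation.** 400,000 patients per arm, with scores at pre-NF and weeks 1, 6, 11 and 16. The benefit grows linearly to week 16. Patients are excluded when their rise from pre-NF passes one cutoff common to both arms. The changed treatment is assumed not to alter the week-16 score. The missing week-16 score is imputed within arm by regression on the four earlier scores. Only the event that triggers exclusion varies between rows.

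| Trigger for exclusion | Correlation | Estimated effect at 5 / 10 / 15% |
|---|---|---|
| Rise recorded at week 11 | equal, 0.3 | 0.51 / 0.51 / 0.51 |
| Unrecorded rise at week 13.5 | equal, 0.3 | 0.50 / 0.50 / 0.49 |
| Unrecorded rise at week 13.5 | equal, 0.6 | 0.49-0.50 / 0.49 / 0.48 |
| Unrecorded rise at week 13.5 | decaying, 0.6 or 0.8 per 5 weeks | 0.49 / 0.47 / 0.46 |
| Week-16 rise itself (limit) | equal, 0.3 | 0.45 / 0.41 / 0.37 |

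With no true effect, the estimate is 0.00 to within simulation error in every row.

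**Size of the loss for a crisis between visits.** It runs from (0.51 − 0.50)/0.51 ≈ 2% to (0.51 − 0.46)/0.51 ≈ 10%.

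**Mechanism.** In the limiting row at 15% overall, the identical arm-blind cutoff removes about 21% of controls and 9% of mbNF patients.

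**The case against.** The strongest reply is that this is a silence and not a prohibition. Exclusion is discretionary, and no sentence says that assessments stop. Several conditions must all hold: instability, a treatment change needed or strongly wanted, that change being a contraindication, a decision to exclude, and all of this before week 16. The 15% case would assign 27 of the roughly 53 expected losses, about half, to this one route, which is high. Scores taken before exclusion remain and feed the imputation. Treatment changes are also captured: "Treatment prior to and during the study will be recorded and explored in analyses", and each assessment asks about "use of scheduled and unscheduled mental healthcare resources outside the study". Finally, patients in crisis may decline the invitation.

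All of that stands, and it limits the size of the problem. It does not supply a route to the week-16 score. Recording a treatment change is not the same as measuring the outcome after it. Imputation from earlier scores is adequate only if they already showed the decline, and with visits about five weeks apart they may not.

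A reader might infer that a quarter or more of a true benefit could be missed, since (0.51 − 0.37)/0.51 ≈ 27%. The documents do not support that as an expectation. It needs exclusion to depend on the week-16 value itself, whereas the exclusion in question happens before week 16. It is a limit only. A reader might also infer a risk of a false positive result. In this model, with one rule applied blind to arm, there is none.

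**Conclusion.** The gap is real and narrow. Section 6.5 permits exclusion from the study for a reason bound up with the primary clinical outcome, and the protocol's own promise of continued assessment does not reach those patients.

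Its frequency cannot be derived from the protocol. On the stated assumptions the consequence runs from no bias, when the worsening was recorded, to an understatement of roughly 2-10% of a true 0.51 SD effect, when a crisis between visits goes unrecorded. The bias would be smaller if the changed treatment brought week-16 scores back down. A null effect stays null.

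This is a cheap improvement worth making because the lost scores cannot be recovered later. It is not a defect that undermines the primary analysis.

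**What to change.** In the Trial Safety paragraph of section 6.5, and under the study-level termination line in section 4.3.2, state that:

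- a treatment change of this kind may end the study intervention, but unless the patient withdraws consent they are still invited to the scheduled BSL-23 assessments, at minimum the one at week 16, with the usual risk checks;
- debriefing and unblinding (section 5.1, Randomization and control condition) wait until that patient's last assessment, because BSL-23 is self-reported.

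Treatment decisions stay with the patient's own providers, and the DBT-group termination rule needs no change.

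**Cost.** The week-16 minimum is BSL-23 (5 minutes), UWRAP (10-30) and C-SSRS (30), or 45-65 minutes. For a patient excluded straight after NF, the full remaining surveys in section 5.2 take 4 × 30 + 2 × 30 = 180 to 5 × 30 + 2 × 45 = 240 minutes. If UWRAP and C-SSRS come on top at 40-60 minutes per timepoint, they add 6 × 40 = 240 to 7 × 60 = 420 minutes, for a total of 420-660 minutes (7-11 hours). Later exclusion costs less. Retained patients on changed treatment add some noise, and their treatment changes must be reported. Assessing patients who may be unstable also draws on the existing clinician risk cover.
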